## Abstract

**Background:** Heart failure (HF) is one of the major causes of mortality worldwide, representing the terminal stage of several cardiovascular diseases. Exercise-based rehabilitation is a beneficial therapy for patients with chronic heart failure (CHF). However, there is a lack of specific guidance on clinical decision-making regarding optimal exercise intensity. It is necessary to optimize the clinical recommendations for HF exercises. We will evaluate the efficacy and safety of different aerobic exercise intensities in patients with heart failure with reduced ejection fraction (HFrEF): the HF-EI trial. This trial aims to assess the appropriate exercise intensity for patients with HFrEF.

**Methods:** After a baseline assessment to determine the safety of exercise, 180 patients will be randomly assigned to supervised high-intensity exercise training (ET) group, supervised moderate intensity training (MIT) group, and control group at a ratio of 1:1:1. Patients randomly receiving high intensity training (HIT) undergo supervised ET (3 times/week, 30 min) for aerobic endurance at 70% peak oxygen consumption (peak VO_2_) intensity for 12 weeks. The MIT patients will perform supervised aerobic ET (3 times/week, 35–42 min) at the anaerobic threshold (AT) intensity for 12 weeks. The control group will continue to maintain their daily activities and will not receive ET. During the baseline and follow-up period, physical examination, laboratory tests, cardiology diagnostic tests, cardiopulmonary exercise tests (CPET), 6-min walk distance (6MWD), scale scores, exercise steps, medications, and clinical events will be monitored. Throughout the research, sport bracelets and patient diaries will be used to monitor and record overall physical activity, training courses, and compliance.

**Discussion:** The HF-EI trial will evaluate the effects of different aerobic exercise intensities on peak VO_2_, quality of life (QoL), and clinical events among patients with HFrEF. The findings of this trial will provide a basis for formulating exercise prescriptions for patients with HFrEF.

**Clinical Trial Registration:**http://www.chictr.org.cn/, identifier: ChiCTR2000036381.

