According to the grading standards for exercise intensity proposed by the 2020 European Society of Cardiology (ESC) Guidelines on sports cardiology and exercise in patients with cardiovascular disease, the anaerobic threshold (AT) intensity is moderate, 70% PeakVO_2_ intensity is high intensity (36). We will design a three-arm randomized controlled experiment to explore the effectiveness and safety of moderate exercise intensity (AT intensity) in the treatment of HFrEF. The HIT (70% PeakVO_2_ intensity) group served as the active control group, and the daily activity group served as the placebo control group. Mainly compare MIT and HIT, or MIT and daily activities, and explore the dose-effect relationship of exercise intensity on changes in clinical outcomes through regression analysis. We assume that MIT has a greater impact in the main results than HIT and daily activities.

We will evaluate the efficacy and safety of different aerobic exercise intensities in patients with HFrEF: the HF-EI trial. This study is the first multicenter randomized controlled trial (RCT) on the effects of different aerobic exercise intensities in patients with HFrEF in China. By collecting data on exercise capacity and exercise rehabilitation, we will evaluate the clinical efficacy of exercise-based CR in Chinese patients with HFrEF. Finally, suitable exercise intensity will be recommended for the popularized HFrEF aerobic exercise program for Chinese patients with HFrEF.

The primary objective of the HF-EI trial is to investigate the effects of different exercise intensities on exercise capacity and quality of life in patients with HFrEF. As secondary objectives, the HF-EI trial will evaluate AT oxygen uptake, 6-min walk distance (6MWD), left ventricle ejection fraction (LVEF), N-terminal prohormone of brain natriuretic peptide (NT pro-BNP), the Patient Health Questionnaire-9 (PHQ-9), General Anxiety Disorder-7(GAD-7), all-cause mortality, HF hospitalization, major cardiovascular events, and adverse events.

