## Methods/Design

### Design

This will be a multi-center, parallel, three-group RCT to evaluate the efficacy and safety of MIT for HFrEF. Eligible participants will be randomly assigned to the HIT intervention group receiving a 12-week supervised training sessions (70% PeakVO_2_ intensity) plus usual medications, MIT intervention group receiving a 12-week supervised training sessions (AT intensity) plus usual medications, or a control group receiving only the usual medication and maintain daily activity. This study has a 12-week intervention and a 12-month follow-up period. Figure 1 shows the study design flow chart. This protocol follows the Standard Protocol Items: Recommendations for Interventional Trials (SPIRIT) guidelines and fulfills the SPIRIT checklist (Supplemental File 1); A SPIRIT checklist is provided in Figure 2 (37).

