### Outcome Measures

The primary outcome for the HF-EI trial is the change in peak VO_2_ and Minnesota Living with Heart Failure Questionnaire scores (MLHFQ)after 12 weeks. We choose the common primary outcomes in order to obtain the comprehensive effect of different exercise intensities on HFrEF treatment. Aerobic exercise has a well-known positive effect on patients with HFrEF in exercise capacity and quality of life, and peakVO_2_ is an important indicator for evaluating the prognosis of HF (22, 40).

Secondary outcomes included, AT oxygen uptake, 6MWD, LVEF, NT pro-BNP, PHQ-9, GAD-7, all-cause- mortality, hospitalization events for HF, major cardiovascular events, and adverse events.

The test indicators require patients to be measured at the hospital rehabilitation center. The test details are as follows:

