### Statistical Methods

The calculation of the sample size will be based on the primary outcome of the RCT. The sample size calculation was performed using PASS V11.0 (NCSS Company of the United States) with the following calculation formula:

$$\begin{array}{l} n=\Psi^{2}\left[\sum_{i=1}^{k}s_{i}^{2}/k\right]/\left[\sum_{i=1}^{k}{\left({\bar{X}}_{i}-\bar{X}\right)}^{2}/\left(k-1\right)\right]\left(k\;=\;3\right) \end{array}$$

The parameters are set to double-sided α = 0.05, β = 0.1, Power = 1–β = 90%, the average difference in peak VO_2_ of the three groups were 0, 2, 4(ml/kg/min) and the average difference in MLHFQ of the three groups were 2, 12, 10. The corresponding standard difference values of peakVO_2_ were 6, 4, 6 (ml/kg/min) and MLHFQ were 5, 18, 16.

The parameter estimation is based on the results of previous researches (22, 42, 43).

A total of 180 cases were required for the three groups, 60 patients in each group, considering the 20% loss to follow-up rate and stratification factors. Because each of the primary endpoints can be individually reflected in clinical significance. Therefore, if one of the two primary endpoints of the intervention group improves significantly, the study is successful.

Blinded statistical analysis will be performed by qualified statisticians using PASW Statistics 18.0 (IBM SPSS Inc., Armonk, New York, USA). The measurement data will be expressed as mean ± standard deviation (x ± s), measurement data by *t* test, and count data by chi-square test. The clinical events of the treatment groups will be statistically compared, according to the principle of intention-to-treat. The Kaplan–Meier method will be used to calculate the cumulative event rate. The event time of all patients will be measured starting from the randomization time (time zero). We will collect all available information on clinical events until the last patient contact, including patients who withdraw consent or those lost to follow-up. Relative risk (RR) will be calculated using the Cox proportional hazard model. If a sufficient number of events occur, the Kaplan–Meier curve will be used for stratified analysis of the exercise group, and the log-rank test will be used to test the difference in survival. The significance level will be set at *p* < 0.05.

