AT relates to the point when the exercise load increases to a certain amount and the tissue demand for oxygen exceeds the amount that the circulation can provide, and the tissues undergo anaerobic metabolism to provide more energy. The critical point from aerobic metabolism to anaerobic metabolism is called AT, expressed as the threshold oxygen consumption of anaerobic metabolism (VO_2_ AT), equivalent to 50–60% of peak oxygen consumption, and directly detected by CPET (44). The advantages of using AT as the basis for formulating exercise prescriptions are sub-maximal exercise intensity, which can prevent the continuous increase of lactic acid levels, avoid hyperventilation and shortness of breath, avoid metabolic alkalosis, reduce the occurrence of overload on the heart and arrhythmia, and ensure high safety. Aerobic exercise with the intensity of the AT has protective effects on CHF, confirmed by the literature (45). For patients with HFrEF, exercise intensity is a range, not a point; AT belongs to sub-maximum medium intensity. Although 70% of peakVO_2_ is high- intensity, it is not ultra-high intensity. This study will explore the effects of these two different intensities.

AT intensity has not been widely accepted internationally. This study compares the effectiveness and safety of AT intensity and high intensity in patients with HF, and aims to reflect the superiority of AT intensity exercise. It has reference value for other colleagues in the world.

Limitations of the study should be recognized as follows: lost to follow-up, influencing factors including patient age, difficulties attending appointments, concurrent illnesses, and the nature of the intervention that made blinding impossible. We made every effort to ensure that evaluators, laboratory technicians and statisticians remain unaware of the treatment allocation.

Altogether, the results of the HF-EI trial may provide evidence on the effective delivery of a contextually adapted exercise-based CR program in China. At the same time, it provides evidence of AT exercise intensity for the world's CR field.

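### The success rule names no arm, comparator or contrast, so the trial can be declared successful on exercise versus daily activities with no difference between MIT and HIT

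*Protocol article*

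**What the plan says.** The rule is one sentence in Statistical Methods: "if one of the two primary endpoints of the intervention group improves significantly, the study is successful". It speaks of a single intervention group and gives no comparator.

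Other sections bear on how to read it, and they do not agree:

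- **Design** describes HIT and MIT in parallel, each as an intervention group, against one control: "plus usual medications, MIT intervention group receiving a 12-week supervised training sessions (AT intensity) plus usual medications, or a control group". The Intervention Group section also covers both exercise arms.
- **Introduction** gives HIT a different role. The HIT "group served as the active control group, and the daily activity group served as the placebo control group".
- **Introduction** names the contrasts of interest, joined by an alternative: "Mainly compare MIT and HIT, or MIT and daily activities".
- **Introduction** states the hypothesis: "We assume that MIT has a greater impact in the main results than HIT and daily activities".
- **Abstract** states the purpose: "This trial aims to assess the appropriate exercise intensity for patients with HFrEF". The **Discussion** adds that the study "aims to reflect the superiority of AT intensity exercise".
- **Outcome Measures** treats the benefit of exercise as established: "Aerobic exercise has a well-known positive effect on patients with HFrEF in exercise capacity and quality of life".

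The planned analysis of continuous outcomes is a t test at p < 0.05, with no pair of arms named.

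**The concern.** A success rule should identify the claim that a positive result supports. This one leaves the arm, the comparator and the contrast open. The conflicting role of HIT means that the rest of the article does not settle them.

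The main consequence is that exercise versus no exercise is enough. If both exercise arms count, HIT or MIT beating control on either endpoint meets the rule. If only MIT counts, MIT beating daily activities on either endpoint meets it. Neither result says anything about whether AT intensity differs from 70% of peak VO2, which is the distinguishing question of the trial. A trial reported as successful could then be cited for AT intensity with no evidence on intensity.

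**Working it through.** **Inputs (Statistical Methods).** Two-sided alpha 0.05 and 90% power. Peak VO2 changes 0, 2, 4 with SDs 6, 4, 6. MLHFQ changes 2, 12, 10 with SDs 5, 18, 16, read as the size of improvement. 60 per arm, 20% loss, so 60 × 0.8 = 48 evaluable per arm.

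**Assumption.** The article does not say which group each planning value belongs to. The first listed is taken as control. Which exercise arm is second does not affect the powers below.

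**1. The plan's own figure.** The printed formula is n = Ψ² × (mean variance) / (between-group mean square).

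- Peak VO2: mean variance (36 + 16 + 36)/3 = 29.33; between-group mean square (4 + 0 + 4)/2 = 4. With Ψ = 2.52, n = 6.35 × 29.33/4 = 46.6. The exact noncentral F calculation gives 48.
- MLHFQ: mean variance (25 + 324 + 256)/3 = 201.67; between-group mean square (36 + 16 + 4)/2 = 28. With Ψ = 2.52, n = 45.7. The exact calculation gives 47.
- With 20% loss: 48/0.8 = 60 per arm, 180 in total; 47/0.8 = 58.75, so 59 per arm, 177 in total.

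The stated 180 reproduces. It is the size for a global three-group test, which can be significant without any difference between MIT and HIT.

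**2. Exercise versus control, MLHFQ, 48 per arm (Welch t test).** Noncentrality = difference / √((s₁² + s₂²)/48).

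- Difference 10, SDs 5 and 18: 10/√(349/48) = 10/2.70 = 3.71; power 0.954.
- Difference 8, SDs 5 and 16: 8/√(281/48) = 8/2.42 = 3.31; power 0.901.

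So a single exercise-versus-control comparison on one endpoint meets the rule with about 90% to 95% probability.

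**3. MIT versus HIT, 48 per arm.** The planning difference is 2 on each endpoint.

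- Peak VO2, SDs 4 and 6: 2/√(52/48) = 2/1.04 = 1.92; power about 48%. For 90% power, 137 evaluable per arm, or 172 enrolled per arm and 516 in total.
- MLHFQ, SDs 18 and 16: 2/√(580/48) = 2/3.48 = 0.58; power 8% to 9%. For 90% power, 1,524 evaluable per arm, or 5,715 enrolled in total.

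These use alpha 0.05 with no multiplicity adjustment.

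**4. Both together.** Simulation with 48 per arm, 10,000 runs per setting and assumed endpoint correlations of 0, 0.3 and 0.6, counting either exercise arm against control on either endpoint:

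| Scenario | At least one significant result versus control | The same, with no significant MIT–HIT difference on either endpoint |
|---|---|---|
| Equal exercise means (assumed: peak VO2 3 and 3, MLHFQ 11 and 11; control 0 and 2) | over 99% | about 90% |
| The plan's own means | over 99% | 44% to 47% |

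**Sensitivity to the order.** If control were second listed, the exercise arms would differ by 4 and 8, with about 90% power on both endpoints; but one exercise arm would then do worse than control on both. If control were third, the exercise arms would differ by 2 and 10 (about 48% and 96%), but control would have the largest gain in peak VO2. Neither order fits the stated expectation of benefit from exercise.

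**The case against.** The strongest reply is that the Introduction does supply comparators. It calls HIT the active control and daily activity the placebo control, and lists MIT versus HIT or MIT versus daily activities as the main comparisons. The Design section also opens by describing a trial of the efficacy and safety of MIT. On that reading the intervention group is MIT, and HIT versus control is not a route to success. This is a fair reading, but the same Design section calls HIT an intervention group, the two contrasts are joined by an alternative, and nothing ties them to the success rule. Even if it is accepted, MIT versus daily activities on one endpoint is sufficient.

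Three stronger readings are tempting, and the documents do not support them:

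- **That the rule tests the wrong contrast.** MIT versus daily activities is itself a stated main comparison, and the Introduction also aims to evaluate exercise-based rehabilitation in Chinese patients. MIT versus HIT is the distinguishing question, not the only one. The trial can succeed without a difference in intensity; it does not have to.
- **That a before-after gain within one arm is the intended criterion.** The word used for improvement permits it literally, but the sample-size formula compares three groups, and the section on trial management speaks of differences in efficacy among the three groups. A between-arm reading is much the more natural.
- **That the sponsor will present any success as support for AT intensity.** No section links the word successful to such a recommendation. That is a risk left open by the wording, not a stated plan.

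The brevity of a journal article is no defence here, because the rule is printed, not left out.

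**Conclusion.** The point holds in this form: the success rule does not identify the arm, the comparator or the contrast; the role of HIT is contradictory; and exercise versus daily activities alone can satisfy the rule although the hypothesis and aim include superiority of AT intensity over HIT.

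At the planning values, the rule is met on MLHFQ against control with about 90% to 95% probability from one comparison, while the intensity comparison has about 48% power on peak VO2 and 8% to 9% on MLHFQ. These figures assume that control is the first listed group and that 48 per arm are evaluable. The simulated percentages also rest on the assumed correlations and, for the first scenario, on assumed equal exercise means. The defect in the wording depends on none of these. The total of 180 is not an arithmetic error; its 90% power does not extend to MIT versus HIT.

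**What to change.** Reconcile the role of HIT between the Introduction and the Design section, and replace the success sentence with wording such as:

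*Success is judged on the between-arm difference in change from baseline to 12 weeks; improvement means a rise in peak VO2 and a fall in MLHFQ score. MIT better than daily activities supports a claim that MIT is efficacious. A claim that AT intensity is superior or preferable requires MIT better than HIT. HIT versus daily activities is supportive. Change within an arm is descriptive.*

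Also state which planning value belongs to which group, and that the 90% power refers to the global three-group test.

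**Cost.** Only text changes, best made before outcome data are seen; the article reports that the trial was still recruiting. The substantive cost is that success against control will no longer support a claim about intensity, and that the sponsor must acknowledge the low power for MIT versus HIT at 180 patients. A non-significant MIT–HIT result at this size should not be presented as showing that the two intensities are equivalent.

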### Randomization and Allocation

We will use a block- randomization, stratified in groups for center to assign participants to the high- intensity exercise group, moderate- intensity exercise group and the control group in a 1:1:1 ratio. For the hierarchical random assignment operation, the statistical unit responsible adopted the SAS version 9.2 statistical software (procedure 'PROC PLAN') to complete program writing and randomization operations. The random distribution results will be released through the network of a central random distribution system. The results of random allocation will be managed by a person designated by the research group, and the results will be executed independently by clinicians. Due to the interventional study design, blinding is impossible for patients and clinical operators. However, the examiners, researchers collecting data on outcome indicators, data managers, and statisticians will be blinded.

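### Success on either of two primary endpoints at an unsplit p < 0.05 gives a two-sided false-positive rate of about 9–10% for one comparison and 16–17% for the two comparisons the protocol names

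*Protocol article*

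**What the plan says.** Outcome Measures names two primaries: "The primary outcome for the HF-EI trial is the change in peak VO_2_ and Minnesota Living with Heart Failure Questionnaire scores (MLHFQ)after 12 weeks". Statistical Methods makes either one sufficient: "if one of the two primary endpoints of the intervention group improves significantly, the study is successful". The reason given is that each endpoint has clinical meaning by itself.

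For the analysis, the same section specifies "measurement data by *t* test, and count data by chi-square test" and then "The significance level will be set at *p* < 0.05". The Introduction states which comparisons matter: "Mainly compare MIT and HIT, or MIT and daily activities". Randomisation is 1:1:1 to three arms.

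The sample-size paragraph uses "The parameters are set to double-sided α = 0.05, β = 0.1, Power = 1–β = 90" per cent, and applies this to peak VO2 and MLHFQ alike. The article mentions no division of alpha, testing order or three-group test that must be passed before the t tests.

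**The concern.** When either of two endpoints can make the trial a success, there are two chances of a false positive for every pair of arms compared. That each endpoint matters clinically is a reason to have two primaries. It does not control error, because the either/or rule is exactly the case in which alpha has to be shared. A t test compares two arms, so in a three-arm trial the t tests are pairwise, and the Introduction names two pairs. On that reading there are four chances of success, each at 0.05.

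The trial is meant to support a recommendation on exercise intensity. A positive result under this rule would be reported at 5% but would not carry that error rate.

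**Working it through.** **Inputs from Statistical Methods.** Planned mean changes are 0, 2, 4 (peak VO2) and 2, 12, 10 (MLHFQ). SDs are 6, 4, 6 and 5, 18, 16. Alpha is two-sided 0.05, power 90%, loss 20%, with 60 patients per arm. Evaluable per arm: 60 × 0.8 = 48. The correlation between the endpoints is not given; I assume 0 to 0.5.

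**Step 1: reproduce the sample size.** One-way ANOVA with three groups, mean variance, noncentrality λ = n × Σ(mean − grand mean)² / mean variance.

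- Peak VO2: mean variance (36 + 16 + 36)/3 = 29.33; sum of squares 4 + 0 + 4 = 8. At n = 48, λ = 48 × 8/29.33 = 13.1 and power is 90.4%. 48/0.8 = 60 per arm, 180 in total: an exact match.
- MLHFQ: mean variance (25 + 324 + 256)/3 = 201.67; sum of squares 36 + 16 + 4 = 56. The requirement is n = 47, and 47/0.8 = 58.75, so 59 per arm.

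So 180 rests on the full 0.05 for each endpoint.

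**Step 2: chance of at least one significant result with no true effect.** For one pair and independent endpoints, 1 − 0.95² = 9.75%. Pairs that share an arm are correlated, so the other cases were simulated with t tests at 48 per arm (equal SDs, 200,000 trials):

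| Comparisons, two endpoints | Correlation 0 | 0.3 | 0.5 |
|---|---|---|---|
| MIT vs control | 9.7% | 9.5% | 9.0% |
| MIT vs control and MIT vs HIT | 17.2% | 17.0% | 16.1% |
| All three pairs | 22.8% | 22.5% | 21.3% |

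Check on the last row at correlation 0: one endpoint with three pairs gives 12.14%, and 1 − (1 − 0.1214)² = 22.8%. With the planning SDs, the rows are 9.5/9.6/9.3%, 16.9/16.5/15.8% and 22.3/21.8/20.9%.

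**Step 3: count improvement only.** The nominal rate for one test is then 2.5%. For MIT vs control on two independent endpoints, 1 − 0.975² = 4.9%. Simulated, with correlation from 0 to 0.5: 4.9% to 4.5% for MIT vs control, and 8.9% to 8.1% for the two named pairs.

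**Step 4: suppose a three-group F test at 0.05 per endpoint came first.** The analysis text does not say this. It would still leave about 9–11% across the two endpoints.

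**The case against.** The strongest objection is that a separate analysis plan may adjust for multiplicity. That would answer an omission, but here the article itself fixes the either/or rule, the 0.05 threshold and a sample size at full alpha. A later plan that split alpha would change the stated basis both for success and for the 180 patients.

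A second objection is that two-sided rates count harm as success, although the rule speaks of an endpoint that improves. This stands, and it is why both sets of figures are given. Judged on improvement alone, the inflation is about two- to fourfold over 2.5%.

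A reader might infer that the error is 23%. That needs HIT against control as a third route to success. The Introduction does not name it among the main comparisons, and the Design section describes the trial as an evaluation of MIT.

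A reader might also infer that a within-arm change suffices, since the rule does not say what the intervention group is compared with. The documents do not support this: the Introduction names between-group comparisons and the sample-size formula is a between-group one. The wording is loose and worth closing, but that is not a source of error to be added here. Nor does the fact that patients who complete the MLHFQ are unblinded bear on alpha; the article already acknowledges that blinding is not possible for them.

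Finally, pairwise testing is inferred, since the text says only t test. Step 4 shows that the more generous reading does not restore 5%.

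**Conclusion.** The point holds as a fault in stated text. The either/or rule at an unsplit 0.05 gives a two-sided false-positive rate of about 9–10% if only MIT against control counts, and about 16–17% for the two named comparisons. It reaches 21–23% only if HIT against control is counted as well. If only improvement counts, the first two are about 4.5–5% and 8–9% against 2.5%.

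These figures assume 48 evaluable patients per arm, no true effect on either endpoint and a correlation of 0 to 0.5. A stronger correlation lowers them without removing the problem: at 0.7 the two-sided rates are 8.4% for one pair and 14.9% for the two named pairs. No reading of the text examined here brings the error back to its nominal level.

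**What to change.** Amend the wording, before any comparative result is seen, as follows.

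1. State success as a between-group difference favouring the tested arm.
2. Split alpha across the endpoints, two-sided 0.025 each, so that the total is at most 0.025 + 0.025 = 0.05. Holm or Hochberg is an alternative, but the plan must then fix the level of the pairwise tests. If the second endpoint moves to 0.05 while pairwise tests on the first still run at 0.025, the pairwise claims together could carry up to 0.075.
3. Within each endpoint, use a three-group test that allows unequal variances (Welch). With MLHFQ SDs of 5, 18 and 16, a pooled F test at nominal 0.025 rejects about 3.3% of the time under no effect.
4. Only if that test is significant, run unequal-variance pairwise t tests at the same level, keeping both MIT vs control and MIT vs HIT. With three groups this is a closed procedure.

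The cost is in power. By the plan's own formula, 48 per arm gives about 85% per endpoint at 0.025 (84.6% peak VO2, 85.3% MLHFQ), down from 90%. Simulated with the planning SDs, power at 0.025 is:

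| Three-group test | Peak VO2 | MLHFQ |
|---|---|---|
| Pooled F | about 81% | about 91% |
| Welch | about 74% | about 98% |

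The Welch test is significant on at least one endpoint about 99% of the time. That is not power for a named pair: for two arms whose peak VO2 means differ by 2, a t test with 48 per arm has about 49% power at 0.05 and about 38% at 0.025.

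Keeping 90% on peak VO2 by the plan's formula would need 56 evaluable per arm: 56/0.8 = 70 per arm, 210 in total. If 180 is kept, only the wording and the power statement change.

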#### Baseline Data

We will monitor the demographic data, medical history, physical status, laboratory tests (NT pro-BNP), cardiology diagnostic tests (LVEF), cardiopulmonary exercise tests (peak VO_2_, AT oxygen uptake), 6MWD, scale score(MLHFQ, PHQ-9, and GAD-7)and medications during the baseline period. Baseline data will be collected through outpatient consultation and medical record review.

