#### Outcome Assessments

Physical examination, exercise steps, medication use, and clinical events (all-cause-mortality, hospitalization events for HF, major cardiovascular events, and adverse events) will receive outpatient follow-up in the 4th and 8th weeks after random assignment. At 12 weeks after randomization, physical examination, laboratory tests, cardiology diagnostic tests, cardiopulmonary exercise test, 6MWD, scale scores, exercise steps, medication, and clinical events will receive outpatient follow-up visits. 4–12 months after randomization, clinical events will be followed up by telephone every month. Both the baseline survey and follow-up will be conducted by two physicians.

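### The blanket mean ± SD and t test suit NT-proBNP poorly: if its values are right-skewed, power is lost and the summary misleads, by an amount that depends on a spread the protocol does not give

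*Protocol article*

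**What the plan says.** Outcome Measures lists NT-proBNP among ten secondary outcomes: "Secondary outcomes included, AT oxygen uptake, 6MWD, LVEF, NT pro-BNP, PHQ-9, GAD-7", followed by the clinical events. Baseline Data names it as the laboratory test, and Outcome Assessments repeats the laboratory tests at week 12 ("At 12 weeks after randomization, physical examination, laboratory tests").

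For continuous data, Statistical Methods gives a single summary ("The measurement data will be expressed as mean ± standard deviation") and a single comparison ("measurement data by *t* test, and count data by chi-square test"). It names no transformation, normality condition, rank test or median-based summary, and makes no exception for any outcome. No other section gives NT-proBNP its own analysis. The article also does not say whether the t test is applied to the week-12 value or to the change. Outcome Measures speaks of change only for the two primary outcomes.

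**The concern.** NT-proBNP cannot fall below zero and has no practical upper limit. The trial enrols NYHA classes I to III and excludes for kidney function only below an eGFR of 30, so a long right tail is to be expected. A few very high values then dominate the raw mean and SD, and they dominate the change score even more. A proportional reduction shared by most patients can be hidden by the scatter of those few.

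At stake is the precision and readability of the only laboratory marker among the named secondary outcomes. This differs from detail that an article leaves to a later document: a method is stated, it covers this outcome, and a standard alternative would do better with data already being collected.

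**Working it through.** **The plan's own figure.** The documents give no effect, SD or power for NT-proBNP. The only figure to reproduce is the sample size, which rests on the primary outcomes. For peak VO2 (means 0, 2, 4; SDs 6, 4, 6):

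- mean variance = (36 + 16 + 36)/3 = 29.33
- sum of squared deviations of the means = 4 + 0 + 4 = 8
- at n = 48 the noncentrality is 48 × 8/29.33 = 13.09, and the three-group F test at α = 0.05 has 90.4% power (89.7% at n = 47)
- 48/0.8 = 60 per arm, so 180 in total

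MLHFQ needs 47 per arm, or 59 after 20% loss. The stated 180 is reproduced, and 48 per arm is the evaluable size used below.

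**Assumptions for NT-proBNP (none from the documents).** Values are log-normal with log-scale SD σ from 0.5 to 1.2. The correlation ρ between log baseline and log week 12 is 0.6 or 0.8. The true ratio between two arms is 0.70, so the log effect is |ln 0.70| = 0.357. Tests are two-sided at 0.05.

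**Hand check at σ = 1.0, ρ = 0.8.** Power ≈ Φ(effect/SE − 1.96), and √(2/48) = 0.204.

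- Log week-12 value: SE = 1.0 × 0.204 = 0.204; 0.357/0.204 = 1.75; power ≈ 42%.
- Log change: SD = σ√(2(1 − ρ)) = 0.632; SE = 0.129; ratio 2.76; power ≈ 79%.
- Log week 12 adjusted for log baseline: SD = σ√(1 − ρ²) = 0.600; SE = 0.122; ratio 2.91; power ≈ 83%.
- Raw week-12 value: control mean e^0.5 = 1.649 and SD 2.161 (in units of the control median); difference 0.30 × 1.649 = 0.495; SE = 2.161 × √((1 + 0.49)/48) = 0.381; ratio 1.30; power ≈ 25%. Skewness makes this approximation rough; simulation gives 28%.

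**Simulation** (48 per arm, ratio 0.70, 12,000 trials per row, power in %; centre not modelled):

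| σ | ρ | Raw week 12 | Log week 12 | Raw change | Log change | Log, baseline-adjusted |
|---|---|---|---|---|---|---|
| 0.5 | 0.6 | 89.8 | 93.0 | 88.1 | 97.2 | 99.1 |
| 0.5 | 0.8 | 89.9 | 93.0 | 99.0 | 100.0 | 100.0 |
| 0.8 | 0.6 | 46.7 | 58.5 | 40.4 | 67.1 | 76.6 |
| 0.8 | 0.8 | 46.5 | 57.7 | 65.5 | 92.7 | 94.6 |
| 1.0 | 0.6 | 28.3 | 41.0 | 24.6 | 49.8 | 58.1 |
| 1.0 | 0.8 | 28.3 | 40.5 | 40.2 | 78.4 | 82.1 |
| 1.2 | 0.6 | 18.0 | 30.7 | 15.1 | 35.9 | 43.1 |
| 1.2 | 0.8 | 18.4 | 29.5 | 24.2 | 62.7 | 66.5 |

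Repeat runs move these figures by about a point, and the ranges quoted elsewhere allow for that.

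**Separating the two sources of gain.** Like for like, the logarithm alone adds about 3 to 13 points on the week-12 value and about 1 to 38 points on change. The rest comes from baseline adjustment. For example, at σ = 1.0 and ρ = 0.8, log week 12 rises from about 41% to 82% when adjusted.

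**Type I error.** With no true effect, every raw-scale and log-scale test above rejected in about 4% to 5% of trials.

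**The summary statistic.** For log-normal data, mean/median = exp(σ²/2) and SD/mean = √(exp(σ²) − 1). At σ = 0.5, 0.8, 1.0 and 1.2 the mean is 1.13, 1.38, 1.65 and 2.05 times the median, and the SD is 0.53, 0.95, 1.31 and 1.79 times the mean. From σ = 1.0 upward, mean minus SD is negative, which a concentration cannot be.

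**The case against.** **This may be ordinary condensation.** One sentence in an article covers all continuous data, it never says raw scale, and a t test on logarithms is still a t test. The full protocol or analysis plan may treat NT-proBNP separately. It stands that the raw scale is an inference. It is nevertheless the plain reading of mean ± SD with a t test and no exception, so the sentence fixes a poor method for this outcome and is not merely silent.

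**The size is not known.** The documents give no NT-proBNP spread, correlation or expected effect. Several eligibility criteria narrow the spread: LVEF below 0.4, stable symptoms and drug doses for at least two weeks, age and BMI limits, and exclusion of new atrial fibrillation. Nor do they say that change is tested, and change is where the raw scale loses most. All of this stands, which is why results for the week-12 value and for σ = 0.5 are shown.

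**Baseline adjustment is a separate matter.** It would help any continuous outcome, so its share of the gain should not be put down to skewness. That also stands.

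**Stronger readings.** A reader might infer that the NT-proBNP comparison is invalid or biased, or that most of its power is certainly wasted. The first fails because the false-positive rate is not inflated. The second holds only for some combinations of large assumed spread and choice of test. Low power here is also partly because the trial was not sized for this marker: at σ = 1.0 and ρ = 0.6, even the log-change test reaches only about 50%.

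**Conclusion.** The concern holds as one of efficiency and reporting for a single secondary outcome. With log-normal values, 48 per arm and a true 30% reduction:

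- At log SD 0.8 to 1.2 and correlation 0.6 to 0.8, raw-scale power is about 15% to 66% on change or 17% to 48% on the week-12 value, against about 42% to 95% for the baseline-adjusted log analysis.
- At log SD 0.5, it is about 88% to 99% on change or 90% on the week-12 value, against 99% to 100%.

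The adjusted log analysis did at least as well as either raw-scale test in every setting run. The size of the gain rests on the assumed skewness, correlation and effect. NT-proBNP lies outside the sample-size calculation and the success rule, so neither the 180 patients nor the primary conclusions are affected. The change is worth making but is not critical.

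**What to change.** In Statistical Methods, except NT-proBNP from the general rule. Analyse log(NT-proBNP) at week 12 with log baseline value and centre as covariates. Report the between-arm ratio of geometric means with a 95% confidence interval, and summarise each arm by median and quartiles. If a full analysis plan already does this, the article's sentence needs only a cross-reference.

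The cost is one sentence. Baseline values and centre are already recorded, and no extra patients, visits or samples are needed. The article describes the trial as still recruiting; the change should be fixed before any unblinded comparison. The one small downside is that the effect becomes a relative difference, a ratio of geometric means, which is a different quantity from a difference in arithmetic means.
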